## Abstract

**Background:**

Latino children in the US experience high rates of obesity, increasing their risk of subsequent diabetes. There are few clinical trials among low-income, Latino families to test interventions that account for and address their unique situation.

**Methods/design:**

This trial, conducted in a Head Start (early childhood education) setting, randomly assigns children 2–5 years of age who have obesity by CDC (Centers for Disease Control and Prevention) guidelines (at least 95th percentile body mass index) and their parents to one of three conditions: (1) control, (2) parent mentor with an experimental curriculum, or (3) parent mentor with a standard curriculum (active control). We designed the experimental arm (2) using data from positive deviants: low-income, Latino families who had been successful in moving their child toward a healthy weight. Parent mentors are recruited and trained from the Head Start centers. Parent mentors then facilitate the teaching and coaching of parent–child dyads with weekly interactions over the course of a 6-month period. The primary outcome is change in adjusted body mass index z-score at the end of intervention and at 6 months post-intervention. Secondary outcomes include generalized self-efficacy, dietary intake, the home food environment, and reported physical activity.

**Discussion:**

This clinical trial contributes to the field by evaluating parent mentoring interventions that are potentially scalable for a population at high risk for continued obesity and subsequent morbidity and mortality.

**Trial registration:**

This trial was registered on October 31, 2017 (ClinicalTrials.gov identifier: NCT03330743).

**Electronic supplementary material:**

The online version of this article (10.1186/s13063-019-3342-3) contains supplementary material, which is available to authorized users.

## Background

Latino children have significantly higher obesity rates than the US population overall; recent national data show prevalences of 22% for Latino children and 15% for white children [1]. Children of migrant and seasonal farmworkers are at even higher risk given disparities in education and income [2, 3]. Early childhood obesity strongly predicts adolescent and young adult obesity [4, 5] and therefore confers a greater long-term risk for developing diabetes and cardiovascular disease [6, 7].

Effective interventions for early childhood obesity are limited, and primarily multidisciplinary, clinic-based models demonstrate effectiveness [8, 9]. Low-income, Latino families in particular face significant barriers to accessing health care [10]; therefore, the high requisite frequency of interactions for effective behavioral change for obesity [11] becomes a significant pragmatic feasibility challenge. Cultural perceptions and beliefs around weight among Latino families also present a significant challenge to acceptance of an intervention [12, 13], particularly for interventions delivered in a health-care environment [14].

Positive deviance is a complexity science-based approach that identifies individuals who are successful in a particular outcome despite being predicted to fail [15, 16]. Identifying the successful behaviors of positive deviants can inform an intervention for the larger population at risk. We previously identified core characteristics of positive deviants for early childhood obesity in a low-income, Latino population [17]. The potential benefit of using positive deviance is that by identifying strategies that already exist in the community, the intervention may be more scalable and overcome challenges related to cultural beliefs [12].

Parent mentors have been effectively used to encourage behavior change across a broad range of topics [18–20]. Parent mentors reduced asthma-related emergency room visits compared with controls [20], and parent mentors increased health insurance coverage and reduced unmet medical needs [18]. Parent mentors may be effective as they are able to leverage shared experience to identify motivations for behavior change and, with additional training, problem-solve effectively with families. Given the increasing evidence that obesity interventions based on a skills-based model are the most effective [8, 21], parent mentors were chosen as the delivery mechanism for this intervention. In this article, we describe the operationalization of findings from a positive deviance inquiry into a behavioral intervention delivered by parent mentors with planned evaluation of effectiveness via a randomized clinical trial.

## Methods/design

### Overall design and aims

This is a randomized controlled clinical trial testing different behavioral interventions to reduce adiposity among a low-income, Latino, preschool-age population. Parents of 2- to 5-year-old children enrolled in a child-care program for low-income families (Head Start) are recruited to participate. Parent–child dyads are randomly assigned to one of three conditions: control, parent mentor with an experimental curriculum, or parent mentor with a standard curriculum (active control).

### Setting, inclusion criteria, and recruitment

Head Start programs in the US serve low-income families and aim to promote school readiness via both individual learning environments and supporting the family’s health, educational, nutritional, and social needs. This particular Head Start program specifically works with populations of migrant and seasonal farmworkers in Oregon. The centers are located across the state in mixed peri-urban and rural areas where farming occurs, and over 4000 children are enrolled annually. Parents can enroll their children at multiple times during the year. As part of the usual care in this Head Start program, classes, offered at least monthly with child care and dinner provided, address parenting and child development, mental health, and nutrition, among other topics.

Inclusion criteria for parent–child dyads are parents of children who have obesity, defined as a body mass index (BMI) of at least 95th percentile using the Centers for Disease Control and Prevention (CDC) criteria, and are 2–5 years of age. Parents must be older than 21 years of age at the time of enrollment and may be of any weight. Both English- and Spanish-speaking families are eligible. Any child with a significant medical co-morbidity, including seizures, moderate to severe developmental delay, cerebral palsy, or taking medications for attention-deficit/hyperactivity disorder, is excluded given the potential for these to influence diet, physical activity, and growth. Current enrollment in a different obesity intervention program is also an exclusion criterion. Only one child per family may be enrolled in the trial. If more than one child per family presents for enrollment, one of the children is chosen at random for the enrollment and assessment.

#### Parent–child dyad recruitment

Eligible parent–child dyads are identified on the basis of the child’s BMI percentile documented by the Head Start community partner on intake into the program. Parents of eligible children are mailed an information letter with an opt-out postcard for them to return if they do not wish to receive any more contact about the study. If parents do not return the postcard, they are contacted and provided with additional study information via phone, text, or follow-up letter left at their respective Head Start center. If the parent expresses interest, we schedule a first visit where we measure their child’s height and weight and screen for co-morbidities. If both the child and the parent are eligible, the intervention is explained in greater detail, and parents are walked through an informed consent form in their preferred language (English or Spanish). Parents who consent to participate are asked to complete additional surveys (described below) and additional anthropometric measures are obtained on the child. Research staff consent, enroll, and randomly assign participants while blinded to the allocation sequence. Given the children’s age, they are not asked for assent.

#### Parent mentor recruitment and training

Potential parent mentors are identified within each early childhood care center by the Head Start staff as parents who have taken on an active or leadership role within the center. They are then recruited to participate on the basis of interest and availability. All parent mentors have a child attending the center and are required to have conversational-level English and Spanish proficiency. Parent mentors are assigned parent mentees after randomization with the expectation that parents mentor up to 14 parents per month.

All parent mentors undergo two-day training by the research staff. The first day of training covers general mentoring skills, such as active listening and supportive feedback, as well as confidentiality and the logistics of the program. The second day of training is specific to the curriculum they are going to use: either the positive deviance curriculum or the *We Can!* curriculum; each curriculum is described in detail in the following section. In regard to the positive deviance arm, the parent mentors themselves are not positive deviants per se; rather, they receive training in how to mentor other parents on the strategies used by positive deviants. Each potential mentor practices presenting portions of the curriculum. Parents participating in the mentor training are compensated for their time. Research staff observe parents during the training, and the final parent mentors are selected on the basis of the observations of research staff. Criteria used to identify candidates are bilingual fluency, engagement in the training, fidelity to the program content, and active listening skills.

### Intervention design

#### Experimental arm design

The experimental curriculum available in both English and Spanish was developed on the basis of findings from a positive deviance study that identified behaviors and practices from Latino families who were successful in changing their child’s weight status from obese toward a healthy weight [17]. After these behaviors were identified, we used a behavioral intervention mapping approach to create the curriculum for parent mentors to apply with parents in the experimental (positive deviance) arm [22, 23]. The four core behaviors that were identified and developed for this intervention were (1) parent creates a healthy home food environment, (2) parent effectively communicates expectations with other care providers, (3) parent supports small changes to increase children’s outside play time, and (4) parent is consistent about rules related to snacking and food. Intervention mapping attempts to explicitly tie theory and intervention program design through a series of steps that identifies what the behavioral outcomes are and the changes necessary to influence a given outcome [22]. (See Fig. 1 for adapted steps.) In this case, we had identified four core behaviors that we believed were tied to successful weight management in positive deviants; these were our behavioral outcomes (step 2 in Fig. 1).

**Fig. 1 Fig1:**

Flowchart of steps in intervention mapping adapted for this trial. Progress is shown from right to left with positive deviance inquiry informing the behaviors identified in step 2.

Using the approach of intervention mapping, we identified the performance objectives a parent would need to meet in order to achieve the target behavioral outcome, and we broke down the behavior into micro-behaviors, similar to prior applications of intervention mapping (step 3 in Fig. 1) [22, 24]. As an example, the behavior of “parent effectively communicates expectations to other care providers” can be broken into at least six different micro-behaviors (performance objectives): (1) parent identifies priorities related to eating and physical activity, (2) parent expresses positive feelings about communicating expectations, (3) parent expresses confidence that they can identify and elicit goals, (4) parent identifies who providers are, (5) parent expects that providers will listen and try to meet expectations, and (6) parent expresses confidence that they can communicate with providers.

Next, we outlined the personal determinants (e.g., self-efficacy or outcome expectations) that would need to be modified to successfully facilitate the accomplishment of the given performance objective (step 4 in Fig. 1). We developed change objectives from a matrix linking the performance objectives to the determinants. For example, for the performance objective of the parent expresses confidence that they can identify and elicit goals, there are determinants of knowledge, attitude, self-efficacy, outcome expectations, and perceived norms (step 5 in Fig. 1). As an example of the matrix outcome, the change objective for this outcome under self-efficacy would be that the parent expresses confidence that they can communicate with providers.

Finally, we employed behavioral change theory and the best available evidence to guide an intervention affecting those health determinants driving the change objectives (step 6 in Fig. 1). Using the example of self-efficacy around provider communication in the preceding paragraph, we developed specific activities in the intervention to build self-efficacy among participants, such as guided practice, goal setting, and planning coping responses related to provider communication.

The intervention is delivered by using a model previously piloted and shown to be acceptable to Latino families with preschool-age children using parent mentors [19]. The parent mentors then follow up with each parent mentee over the phone, in person, or using text messaging on a weekly basis. This group also receives usual care in their Head Start setting.

#### Comparison arm design

The National Institutes of Health *We Can!* curriculum is used by parent mentors in the active comparison arm. Materials are available in both English and Spanish and this program has been shown to improve knowledge, attitudes, and reported behaviors among parents who have completed it [25, 26]. The curriculum was professionally translated into Spanish and proofed by a bilingual member of the research staff. This group also receives usual care in a Head Start setting.

#### Intervention frequency (intensity)

Parent–child dyads randomly assigned to the control arm receive health information from the Head Start center their child is enrolled in per the center’s usual care practice. Parent–child dyads randomly assigned to either parent mentor arm attend a 1-hour monthly meeting with their parent mentor and the other mentees in their mentoring group. (See Table 1 for a list of topics and activities.) The parents in the mentoring arms also receive individualized coaching on their goals for that month via weekly phone, text, or in-person follow-up with their parent mentor. The two intervention arms have 4 months of group meetings and individual mentoring followed by 2 months of individual mentoring on a weekly basis. The focus for the weekly communication is to encourage the identified behavior change and problem-solve through any potential obstacles faced.

**Table 1 Tab1:** Topics covered in the two active intervention arms with the parent mentor–led curricula

Month	Positive deviance-based curriculum	*We Can!* curriculum
1	Creating a healthy home food environment	Overview, content, and structure of program. Motivation for eating well and moving more.
2	Effective communication around feeding and physical activity	Introducing the concept of energy balance
3	Supporting outside play time	Managing “energy in” of energy balance
4	Providing consistency, specifically around snacking	Managing “energy out” of energy balance
5	Individual goal setting, support, and troubleshooting (no community meeting)	Individual goal setting, support, and troubleshooting (no community meeting)
6	Individual goal setting, support, and troubleshooting (no community meeting)	Individual goal setting, support, and troubleshooting (no community meeting)

### Randomization

Parent–child dyads enrolled in the study are randomly assigned 1:1:1 to usual care, the experimental intervention, or the control intervention. (See Fig. 2 for steps involved in each arm.) REDCap (Research Electronic Data Capture) is used to facilitate randomization upon enrollment. REDCap also facilitates secure data entry and data quality assurance via data entry validation procedures. A block randomization scheme with block size varying from 6 to 12 was generated. Allocation concealment was maintained by having separate personnel review and upload the final allocation tables. Personnel randomly assigning participants are blinded to the actual group assignments derived from the allocation table. We do not blind participants by group assignment after randomization, and assessors at each follow-up are un-blinded.

**Fig. 2 Fig2:**
[figure not shown]
Randomization and flow of participants through trial over time

### Sample size

Given the growth patterns of preschool-age children, weight maintenance has been recommended as the goal as this will lead to a reduction in adiposity with expected linear growth [27]. For the power calculations, we used a mean BMI z-score of 2.5 with a standard deviation of 0.7 for the baseline measurements, based on a previous trial in a similar popuation [19]. A BMI z-score of 2.5 is equivalent to a mean of 120% of the 95th percentile BMI for age and gender. Weight maintenance at this age leads to roughly a 0.5-unit reduction in BMI z-score over 4–6 months among children with obesity, a clinically meaningful reduction. We assumed a standard deviation of 1.0 for the 0.5-unit change in BMI z-score over 6 months. With these assumptions and to achieve 80% power at an alpha of 0.05, we would need 64 children per group to complete the 6-month assessment to detect this clinically meaningful difference of 0.5-unit reduction in BMI z-score between the two active intervention groups. We did not include a repeated measures correlation coefficient in our sample size calculation. We estimated a roughly 25% dropout rate by 6 months given the mobility of the targeted population, and so we aimed to recruit and enroll 80 dyads per group (240 parent–child dyads in total).

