## Discussion

The primary goal of this study is to test the effectiveness of a behavioral intervention informed by a positive deviance approach for obesity reduction in young children. We used a positive deviance approach to identify key behaviors of successful families and then used behavioral intervention mapping to develop the experimental intervention. We employed this approach to identify health behaviors associated with successful weight management already in use by families of this demographic. Consistent with the usual approach of intervention mapping, we applied the method of breaking each behavior into a subset of performance objectives, then identifying health determinants of those performance objectives, and finally designing activities to address those determinants as change objectives. The behavioral intervention mapping approach has been used previously in obesity intervention development [24, 47]. To the best of our knowledge, using positive deviance and behavioral intervention mapping techniques together has not been done previously.

To best examine the effectiveness of the positive deviance approach to intervention development, we included an active comparison arm. This allows us to determine whether the content specifically derived from the positive deviance inquiry results in greater intervention effectiveness. The active comparison arm, *We Can!*, targets more traditional behaviors associated with a healthy diet, whereas the positive deviance curriculum focuses more on parenting skills (being consistent and effective communication).

There are a number of challenges to our approach. First, although our design will allow us to determine the differences in effectiveness of the positive deviance approach over both usual care and traditional comparison, it will result in smaller differences in change between some pairs of the groups, necessitating a larger sample size. However, in conjunction with our community partner, we anticipate being able to achieve our recruitment goal of 240 parent–child dyads. The potential benefit of including the *We Can!* group is that if there is no demonstrated difference between *We Can!* and the positive deviance group, it may be that simply having a parent mentor who provides social support for behavioral change and can reinforce topics is sufficient. The current study design is not a non-inferiority design, however, and cannot evaluate the equivalence of these curricula directly.

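### Enrolling 80 per group does not cover the stated 25% dropout: it leaves 60 completers, not the 64 that the plan says 80% power requires

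*Protocol article*

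**What the plan says.** The Sample size section of the protocol article sets enrolment in three steps.

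- **Completers required.** The plan aims "to achieve 80% power at an alpha of 0.05", for a "clinically meaningful difference of 0.5-unit reduction in BMI z-score between the two active intervention groups". On the variability it says: "We assumed a standard deviation of 1.0 for the 0.5-unit change in BMI z-score over 6 months". From these it concludes that "we would need 64 children per group to complete the 6-month assessment".
- **Dropout.** "We estimated a roughly 25% dropout rate by 6 months given the mobility of the targeted population".
- **Enrolment.** The same sentence continues "and so we aimed to recruit and enroll 80 dyads per group", which it totals as 240 dyads over three groups.

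The Discussion repeats the total: "we anticipate being able to achieve our recruitment goal of 240". The article gives no other dropout rate and no further allowance for loss. The Primary outcome section names the two active arms at 6 months as the primary comparison, so the comparison and time point that were powered are the primary ones.

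**The concern.** The enrolment figure is presented as following from the dropout estimate, yet removing a quarter of 80 does not leave 64. The pattern points to a common slip: the required number was raised by 25% instead of being divided by the 75% expected to remain. The two operations differ because dropout is a fraction of those enrolled, not of those who complete.

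What is at stake is the power claimed for the primary comparison. A reader of the section would conclude that 80% power survives 25% dropout. The requirement of 64 leaves almost no reserve, so any shortfall in completers takes power below target. The article itself treats attrition as a main risk, in the Data analysis section and again in the Discussion.

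**Working it through.** **Inputs, all from the Sample size section:** difference between the two active arms 0.5; standard deviation of change 1.0; alpha 0.05; power 80%; dropout roughly 25%; enrolment 80 per group. Allocation is 1:1:1 (Randomization section), so the primary comparison is 1:1. No repeated-measures correlation was used, so this is a plain two-sample comparison of means. The section does not say whether alpha is one- or two-sided. I take it as two-sided, because that reproduces the plan's 64; one-sided alpha needs only 50 per group by the normal approximation.

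**Step 1: reproduce the 64.** The normal approximation is

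n = 2 × (1.960 + 0.842)² × (1.0 / 0.5)² = 62.8, so 63 per group.

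The exact two-sample t test gives 63.8, so 64 per group, with power 80.1%. The plan's 64 is correct.

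**Step 2: reproduce the 80.**

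- 64 × (1 + 0.25) = 80, the plan's figure exactly.
- 64 / (1 − 0.25) = 85.3, so 86 per group and 3 × 86 = 258 in total.
- 64 / (1 − 0.20) = 80, so the plan's figure is right for 20% dropout.

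Rounding does not explain the gap. Starting from 63 completers, 63 / 0.75 = 84.

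**Step 3: what 80 per group delivers at 25% dropout.** 80 × 0.75 = 60 completers per group, 4 short of 64. With the t test at a standardised difference of 0.5 / 1.0 = 0.5:

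| Completers per group | Power for a difference of 0.5 | Difference detectable with 80% power |
|---|---|---|
| 64 | 80.1% | 0.50 |
| 60 | 77.5% | 0.516 |

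By the normal approximation, power at 60 is 78.2%, against 80.7% at 64.

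**Step 4: allow for the word "roughly".** The article gives no range. Taking 22% to 28% as an assumption, and showing 20% for reference:

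| Dropout | Completers per group, from 80 | Power |
|---|---|---|
| 20% | 64.0 | 80.1% |
| 22% | 62.4 | 79.1% |
| 25% | 60.0 | 77.5% |
| 28% | 57.6 | 75.8% |

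Power stays below 80% over the whole assumed range.

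**The case against.** The arithmetic is hard to dispute, so the case on the other side is about how much it matters.

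1. **The standard deviation is probably cautious.** The plan gives a baseline standard deviation of 0.7 and states: "We did not include a repeated measures correlation coefficient in our sample size calculation". If the standard deviation at follow-up is also 0.7 (an assumption), the standard deviation of change is 0.7 × √(2(1 − r)), where r is the correlation between a child's baseline and 6-month scores. At r = 0 this is 0.99, so 1.0 amounts to assuming almost no correlation. With 60 completers, 80% power needs a standard deviation of at most 0.97, reached at r of about 0.04. Power would be 82% at r = 0.1, 91% at r = 0.3 and 97% at r = 0.5. On that view, four completers matter little beside the uncertainty in the standard deviation.
2. **The analysis may recover some precision.** Multiple imputation, a linear mixed model and a possible baseline covariate are planned in the Data analysis section.
3. **The dropout rate is only approximate,** and the loss is 2.5 percentage points of power.

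The first point has force as a comment on actual power: it may well exceed 80%. It does not repair the statement. The article gives no value of r and takes no credit for one, the 0.7 is not explicitly for the adjusted score used as the outcome, and effects in the other direction, such as mentoring in groups, are not counted either. The second point fails for a similar reason: the 64 is defined as children who complete the assessment, and no gain from the analysis is claimed or quantified. The third point is right that the loss is small, but 80 is the correct answer only at 20% dropout.

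**Conclusion.** The concern holds. On the plan's own inputs, 80 enrolled per group and 25% dropout leave 60 completers per group, against the 64 required. Power for the primary comparison is then 77.5%, not 80%, and the difference detectable with 80% power is 0.52, not 0.50. Meeting the stated requirement would take 86 per group: 6 more in each, 18 more in total.

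This rests on two-sided alpha, on the stated standard deviation of 1.0, and on dropout of 25% in each active arm. It is a statement about the plan's own derivation, not a forecast of the power the trial will have. The consequence is modest and leaves the design, the outcome and the analysis untouched. It still needs correcting, because the power stated for the primary comparison does not follow from the figures printed beside it.

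**What to change.** Keep 240 dyads and correct the sentence in the Sample size section. For example: with 80 dyads enrolled per group and 25% dropout by 6 months, 60 children per group are expected to complete the assessment, which gives 77.5% power for a difference of 0.5 (80% power for a difference of 0.52) at two-sided alpha 0.05. This also settles whether alpha is one- or two-sided.

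Stating that 80 per group tolerates 20% dropout would also be arithmetically correct. It is the weaker choice, because it sets aside the plan's own 25% estimate, which the section justifies by the mobility of the population. If the sponsor prefers to keep 80% power at 25% dropout, the target becomes 86 per group (258 in total), and the 240 in the Discussion must change with it.

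The recommended correction costs one sentence and a slightly less favourable power figure. It needs no extra enrolment and no change to the analysis.
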